### Proposed Analyses

All analyses will be completed using an "intention-to-treat" principle [68] such that data from all subjects will be included in the analysis regardless of their level of adherence to the interventions over the course of the study.

The association between intervention condition (i.e., MFG and CR vs. MFG alone) and relapse will be examined using a chi-square. However, in situations in which the requirements for this analysis are violated (e.g., expected value of any cell ≤ 5), Fisher's exact probability test [69] with the continuity correction proposed by Overall [70] will be used instead.

Per the recommendations outlined by Vickers and Altman [71], the association between intervention condition (i.e., MFG and CR vs. MFG alone) and continuous secondary outcome measures (e.g., caregiver burden and social functioning scores) will be examined using an analysis of covariance with participants' baseline scores on the secondary outcome measure included as a covariate. With regard to the association between intervention condition and categorical secondary outcome measures (e.g., employed vs. unemployed), a chi-square analysis will be used. However, in situations in which the requirements for this analysis are violated, Fisher's exact probability test [69] with the continuity correction proposed by Overall [70] will be used instead.

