### Participants

#### Sample Characteristics

Individuals with first-episode psychosis and their caregiving relatives will be recruited from the Early Psychosis Intervention Center (EPICENTER) at University Physicians Hospital. EPICENTER is an outpatient treatment program that provides evidence-based psychosocial treatments for individuals experiencing their first psychotic episode. Inclusion criteria for participants at EPICENTER are (i) a diagnosis of an affective or schizophrenia spectrum psychotic disorder as determined by the Structured Clinical Interview for the DSM-IV (SCID [27]), (ii) less than 5 years of frank psychotic symptoms as determined by the Symptom Onset in Schizophrenia inventory (SOS [28]), (iii) being between the ages of 18-35, and (iv) willingness to receive treatment at EPICENTER. The durational criteria for psychotic symptoms (< 5 years) is based on the operational definition of first-episode psychosis outlined by Breitborde and colleagues [29]. Individuals with first-episode psychosis are excluded from EPICENTER if they meet criteria for substance-induced psychosis as determined by the SCID, are unwilling or unable to provide informed consent, or meet criteria for a diagnosis of mental retardation. Caregiving relatives are defined as someone with whom the individual with first-episode psychosis maintains considerable face-to-face contact (≥ 10 hours per week). Family caregivers do not need to be biological relatives of the individual with first-episode psychosis. It is anticipated that some individuals with first-episode psychosis will have more than one caregiving relative who wishes to participate in the study; hence, we anticipate recruiting ≈1.5 familial caregivers for each individual with first-episode psychosis.

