#### Number of Participants and Power Analysis

Current recommendations for a priori determination of the number of subjects to include in a study suggest the inclusion of sufficient subjects to maintain adequate statistical power to detect a clinically meaningful effect size [34]. One such measure, Number Needed to Treat (NNT) [35], has been identified as particularly useful in conveying clinical significance and in guiding the design of randomized clinical trials [36]. NNT provides an estimate of the number of individuals who would need to receive a treatment in order to prevent the occurrence of one negative outcome. With regard to family psychoeducation, a recent meta-analysis found that the NTT for this intervention was 8; (95% CI 6-18) [9]. This suggests that this intervention would need to be provided to 8 individuals to prevent one relapse. Although there is no established criteria for a clinically meaningful reduction in NNT [36], for the current study we defined a clinically meaningful benefit of the MFG and CR condition as an NNT one-half the size of the NNT for MFG along (i.e., an NNT for MFG and CR = 4). This value (i.e., NNT = 4) falls outside of the 95% confidence interval of the NNT for family psychoeducation alone as reported in a past meta-analysis [9] and is consistent with the NNT value use to determine a priori statistical power for most randomized controlled trials of interventions for mental illnesses [36]. Using these NNT values and the pwr software package [37] developed for the R statistical platform [38], we determined that 17 families (i.e., individual with first-episode psychosis and caregiving relative[s]) would need to be allocated to both the MFG-CR and MFG alone conditions, respectively, to ensure statistical power of 0.80 (i.e., total sample size = 34). To protect against subject attrition, we will recruit an additional 6 families (i.e., ≈20% of the total sample size), bringing the total sample size to 40.

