### Randomization and Treatment Allocation

Treatment allocation for this study is depicted in Figure 1. Upon enrollment in the project, individuals with first-episode psychosis will be randomized to either the MFG and CR condition or the MFG alone condition. Randomization will be completed using a block randomization procedure with blocks of varying sizes.

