Caregiving relatives of individuals with psychotic disorders have also been shown to experience a reduction in caregiver burden and psychological distress (e.g., depression and anxiety) after participation in family psychoeducation [63,64]. Thus, we plan to conduct additional secondary analyses to examine whether caregivers whose ill relatives are in the MFG and CR group experience greater benefits in these areas as compared to caregivers whose ill relatives are in the MFG alone condition. Caregiver burden will be assessed using the Burden Assessment Scale [BAS] [65], and depression and anxiety will be assessed using the Beck Depression Inventory [BDI] [66] and Beck Anxiety Inventory [BAI] [67], respectively. These measures will be administered upon enrollment to the study and after completion of 12 months of MFG.

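### Caregiver outcomes are assigned ordinary ANCOVA although about 1.5 caregivers share each randomised patient, so standard errors are too small and the false-positive rate exceeds 5%

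*Protocol article*

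**What the plan says.** Four statements in the protocol article bear on this.

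- **Unit of randomisation** (Randomization and Treatment Allocation): "individuals with first-episode psychosis will be randomized to either the MFG and CR condition or the MFG alone condition". Every caregiver of a patient therefore falls in that patient's arm.
- **Caregivers per patient** (Sample Characteristics): "some individuals with first-episode psychosis will have more than one caregiving relative who wishes to participate in the study", and "we anticipate recruiting ≈1.5 familial caregivers for each individual with first-episode psychosis".
- **The caregiver comparison** (Secondary Outcome Measures): the aim is to "examine whether caregivers whose ill relatives are in the MFG and CR group experience greater benefits in these areas". The areas are burden (BAS), depression (BDI) and anxiety (BAI), measured at enrolment and after 12 months of MFG.
- **The model** (Proposed Analyses): "continuous secondary outcome measures (e.g., caregiver burden and social functioning scores) will be examined using an analysis of covariance". The only covariate named is the person's own baseline score. Under the intention-to-treat rule, "data from all subjects will be included in the analysis regardless of their level of adherence".

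The article mentions no family effect, cluster-robust standard error, averaging within families, or rule that selects one caregiver per family.

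**The concern.** ANCOVA takes its standard error and residual degrees of freedom on the footing that the records are independent given arm and baseline. Relatives of the same patient respond to the same illness course and share the same allocation, and each has at least 10 hours a week of face-to-face contact with that patient. Positive correlation between their scores is the natural expectation. About 60 caregivers then carry less information than 60 independent people, while the analysis counts them as 60.

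Confidence intervals for all three caregiver measures would be too narrow. Chance differences between arms would be declared a caregiver benefit more often than the nominal level allows. Benefit to caregivers is a declared secondary aim, so this touches a conclusion that the trial intends to draw.

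**Working it through.** The article gives no figure for the caregiver analyses, so there is none to reproduce. The check asks how far the stated model departs from its nominal error rate.

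**Inputs from the article.** There are 40 families (34 plus 6 for attrition; Number of Participants and Power Analysis), taken as 20 per arm, and about 1.5 caregivers per family. That gives 40 × 1.5 = 60 caregivers.

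**Assumptions.**
- The ICC is not given; 0.1 to 0.7 is shown.
- The spread of caregivers per family is not given. Two patterns with mean 1.5 are used. Pattern A: half the families have one caregiver and half have two. Pattern B: 15 families per arm have one and 5 have three.
- Alpha is not stated; two-sided 5% is used.
- The ICC applies to the residuals after baseline adjustment.

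**Design effect.** For m caregivers per family, DE = 1 + ICC × (Σm² / Σm − 1).
- Pattern A, all 40 families: Σm² = 20×1 + 20×4 = 100 and Σm = 60, so DE = 1 + 0.667 × ICC.
- Pattern B, per arm: Σm² = 15×1 + 5×9 = 60 and Σm = 30, so DE = 1 + ICC.

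The true standard error is √DE times the reported one. The large-sample type I error is 2 × [1 − Φ(1.96 / √DE)].

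**Simulation.** For each setting, 40,000 null trials were run with 20 families per arm, randomisation by family, baseline-outcome correlation 0.5, and caregiver-level ANCOVA.

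| Pattern | ICC | DE | √DE | Type I error, formula | Type I error, simulated |
|---|---|---|---|---|---|
| A | 0.1 | 1.07 | 1.03 | 5.8% | 5.7% |
| A | 0.3 | 1.20 | 1.10 | 7.4% | 7.5% |
| A | 0.5 | 1.33 | 1.15 | 9.0% | 8.9% |
| A | 0.7 | 1.47 | 1.21 | 10.6% | 10.7% |
| B | 0.1 | 1.10 | 1.05 | 6.2% | 6.1% |
| B | 0.3 | 1.30 | 1.14 | 8.6% | 8.4% |
| B | 0.5 | 1.50 | 1.22 | 11.0% | 10.7% |
| B | 0.7 | 1.70 | 1.30 | 13.3% | 13.3% |

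Under pattern A the 60 caregivers are worth 60 / DE = 56, 50, 45 and 41 independent ones at the four ICC values. With 17 families per arm, the number before the attrition allowance, pattern A gives 5.8%, 7.1%, 8.9% and 10.2% (12,000 runs per setting). With ICC set to 0, the error stays near 5%, so the excess comes from the clustering.

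**Check of the remedy.** ANCOVA on family means, one record per randomised patient, gave 4.5% to 5.3% in every setting with 17 or 20 families per arm and ICC from 0 to 0.7 (12,000 runs per setting).

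**The case against.** Three arguments can be made for the plan as it stands.

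**The unit of analysis is inferred.** Proposed Analyses names a model and a covariate but does not say that each caregiver is one record. An ANCOVA on family means is still an ANCOVA, the intention-to-treat sentence is about adherence, and the sample size is counted in families ("17 families (i.e., individual with first-episode psychosis and caregiving relative[s]) would need to be allocated to both the MFG-CR and MFG alone conditions"). This is true as far as it goes. But the stated comparison is between caregivers, all subjects' data are to be used, and no aggregation rule appears. A reader following the text would enter one row per caregiver. If family means were intended, the text has to say so.

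**A short article may leave this to a fuller plan.** It could have left the model open. Instead it assigns a model, uses caregiver burden as an example and fixes the covariate. That model does not fit the data structure described a few sections earlier, so this is a stated choice rather than an omission.

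**The inflation may be smaller than shown.** What counts is the correlation left after baseline adjustment. If the shared family component is stable over the year, the baseline score absorbs part of it. Under pattern A, when the family component correlates 0.5, 0.8 or 1.0 between baseline and 12 months, simulated type I error (20,000 runs) is 7.0%, 6.3% and 5.6% at ICC 0.3, and 9.1%, 7.3% and 6.0% at ICC 0.5. This point stands as a limit on size. It does not change the direction, and a family component less stable than 0.5 would push the figures up.

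**Conclusion.** The concern holds. The stated model ignores the family cluster, and any positive residual correlation between caregivers of one patient makes its standard errors too small.

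The size depends on quantities that the article does not give. With one or two caregivers per family, type I error runs from just under 6% (ICC 0.1) to about 11% (ICC 0.7). If a quarter of families supply three caregivers, it can reach about 13%. A family component that is very stable from baseline brings the figure down to about 6% at ICC 0.3 to 0.5. These figures assume a two-sided 5% test and caregiver-level records.

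Only BAS, BDI and BAI are affected; relapse and all patient-level outcomes are not. It should be corrected before results are seen, but it does not threaten the primary conclusion.

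**What to change.** State in Proposed Analyses that caregiver outcomes are analysed with a linear mixed model: arm and the caregiver's baseline score as fixed effects, a random intercept for family, and Kenward-Roger degrees of freedom because there are only 40 families. The simpler alternative is to run the ANCOVA on the family mean of the outcome, with the family mean baseline as covariate. It uses one record per randomised patient and held its error rate in the check above. Name one of the two in advance as the main analysis.

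The cost is one sentence, with no extra participants, visits or data beyond a family identifier on each caregiver record. Intervals will be somewhat wider: under pattern A, honest standard errors at ICC 0.3 to 0.5 are about 10% to 15% larger than those ordinary ANCOVA would report.

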### Secondary Outcome Measures

Recognizing that recovery from psychotic disorders involves more than just a remission of psychotic symptoms [55], we will also explore the benefit of combining MFG and CR on other outcomes among individuals with first-episode psychosis. These will include social and vocational functioning (Social Functioning Scale: SFS [56]), everyday functioning (brief form of the UCSD Performance-Based Skills Assessment: UPSA [57]), health-related quality of life (RAND 36-Item Health Survey [58]), service utilization (Service Utilization and Resources Form for Schizophrenia: SURF [59]), and independent living status. Independent living status will be assessed using the methodology outlined by Palmer et al. [60]. Per this methodology, subjects' living status will be rated on a 4-point scale ranging from (1) 'totally dependent' (i.e., living in a facility with 24-hour clinical care) to (4) 'independent' (i.e., living alone or with a partner who provides a level of support consistent in typical cohabitation relationships). These measures will be administered when subjects enroll in the study and again after the completion of 12 months of MFG.

Additionally, to replicate findings linking participation in CR to improved cognitive functioning among individuals with psychotic disorders [26], individuals with first-episode will complete the consensus cognitive battery developed by the National Institute of Mental Health's Measurement and Treatment Research to Improve Cognition in Schizophrenia (MATRICS) initiative [61]. Of note, this battery does include a specific assessment of problem-solving skills (i.e., the mazes subtest from the Neuropsychological Assessment Battery [62]). Participants in the MFG and CR condition will complete the MATRICS battery three times over the course of the study: (i) at enrollment; (ii) upon completion of CR intervention, and (iii) upon completion of 12 months of the MFG intervention. Individuals randomized to the MFG alone condition will complete the MATRICS battery three times over the course of the study: (i) at enrollment, (ii) at 10 weeks, and (iii) upon completion of 12 months of the MFG intervention

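### Categorical secondary outcomes are tested without the baseline status that is collected: valid, but less precise when baseline predicts outcome

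*Protocol article*

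**What the plan says.** The Proposed Analyses section of the protocol article has two rules for secondary outcomes, side by side.

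- **Continuous outcomes:** "analysis of covariance with participants' baseline scores on the secondary outcome measure included as a covariate".
- **Categorical outcomes:** "categorical secondary outcome measures (e.g., employed vs. unemployed), a chi-square analysis will be used". If the chi-square requirements fail, Fisher's exact test with Overall's correction replaces it. Neither test has a place for a baseline value.

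The Secondary Outcome Measures section lists the patient measures: social and vocational functioning, everyday functioning, quality of life, service use and independent living status. On timing it says: "These measures will be administered when subjects enroll in the study and again after the completion of 12 months of MFG". For independent living, "subjects' living status will be rated on a 4-point scale", running in order from full dependence to independence. The article does not say whether this rating goes to the continuous or the categorical rule. Nowhere does it plan an adjusted, stratified or change-based analysis of a categorical outcome.

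**The concern.** Employment and living arrangements tend to persist, so a patient's status at enrolment may be a good predictor of status a year later. The plan uses that information for continuous outcomes and leaves it out for categorical ones, without giving a reason. The trial has only 40 patients, or 34 if the attrition allowance is used up, so precision is scarce.

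What is at stake is power on these secondary comparisons, and how a result can be read if the arms happen to differ at baseline. A second, smaller matter is that the handling of the ordered living-status rating is left open. One reading of the text sends it to a test that ignores the order.

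**Working it through.** **Figures in the plan.** The article gives no rate, effect or power for any categorical secondary outcome, so there is nothing to reproduce. Its sample size (17 + 17 = 34, plus 6 = 40) was set for relapse and does not bear on this point. It does fix the two arm sizes worth examining: 20 per arm as recruited, and 17 per arm after the attrition allowance.

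**Assumptions, none of them from the article.** Two-sided 5% level; 35% positive at baseline; control-arm probability of a positive 12-month status 0.80 if positive at baseline and 0.20 if not; a common odds ratio for treatment within each baseline stratum.

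**Implied rates.**
- Control: 0.35 × 0.80 + 0.65 × 0.20 = 0.41.
- Treated, odds ratio 4: the odds of 4 become 16 (probability 0.941) and the odds of 0.25 become 1 (probability 0.50). Overall: 0.35 × 0.941 + 0.65 × 0.50 = 0.654.
- Baseline-outcome correlation (phi) in controls: 0.60 × √(0.35 × 0.65 / (0.41 × 0.59)) = 0.58.

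**Chance imbalance at 20 per arm.** The SD of the baseline difference between arms is √(2 × 0.35 × 0.65 / 20) = 0.151. Carried through the 0.80 - 0.20 = 0.60 gap, this moves the 12-month difference by 0.151 × 0.60 = 0.09.

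**Simulated power, chi-square v baseline-stratified Mantel-Haenszel without continuity correction.**

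| Odds ratio | 20 per arm | 17 per arm |
|---|---|---|
| 2 | 0.10 v 0.14 | 0.12 v 0.12 |
| 4 | 0.32 v 0.42-0.43 | 0.32 v 0.37 |
| 6 | 0.51-0.52 v 0.64 | 0.49 v 0.56 |

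**Dependence on how well baseline predicts outcome** (35% positive at baseline, log odds ratio 1.5, that is an odds ratio of about 4.5).

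| 12-month rate by baseline status | Phi | 20 per arm | 17 per arm |
|---|---|---|---|
| 50% v 30% | 0.2 | 0.58 v 0.60 | 0.56 v 0.54 |
| 65% v 25% | 0.4 | 0.49 v 0.56 | 0.48 v 0.49 |
| 80% v 20% | 0.6 | 0.37 v 0.49 | 0.37 v 0.42 |
| 90% v 10% | 0.8 | 0.19 v 0.33 | 0.20 v 0.29 |

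**Type I error.** Across these settings the chi-square rejects a true null in 0.047 to 0.054 of trials, so it is valid. In the 80% v 20% setting, an absolute baseline imbalance of 15 points or more occurs in about 37% (17 per arm) to 40% (20 per arm) of trials. When an imbalance that large lies in one given direction, the chi-square rejects in about 0.085 of trials at 20 per arm and 0.10 to 0.11 at 17. The stratified test stays near 0.05.

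**Continuity correction.** With it, Mantel-Haenszel power at 20 per arm and odds ratio 4 falls to 0.28, below the chi-square's 0.32. The version of the test therefore has to be named.

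**Living status.** Two arms by four levels make 8 cells, so 40 patients give an average expected count of 40 / 8 = 5. The smallest expected count then cannot exceed 5. Under the limit that the article gives as its example for relapse (an expected count of 5 or less), the analysis would move to Fisher's test. That test also ignores order and baseline.

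**The case against.** The strongest reply is that nothing here is an error. Randomization makes the unadjusted comparison valid, and the calculation above confirms it. A reader might infer that chance baseline imbalance biases these comparisons or passes for a treatment effect. The documents do not support that: the higher rejection rate arises only conditional on an unlucky allocation and is already counted inside the 5%. This part of the reply stands.

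It can also be said that a recommendation cited for continuous outcomes does not bind the plan for binary ones, where adjustment changes the odds ratio being estimated and sparse data are a real difficulty. That is fair. The contrast between the two rules shows an unused opportunity, not a contradiction.

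A reader might further infer that living status will be tested by a 3-degree-of-freedom chi-square on sparse cells. The article does not say so. It never classes the rating as categorical, its only categorical example is employment, and the Fisher fallback would replace a chi-square with small expected counts. What remains is that the method for this rating is not stated.

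Three more limits stand. The article names no instrument for employment; the social functioning or service use measure, both taken at enrolment, is the presumable source. All rates used here are assumed, and the gain shrinks at 17 per arm. The outcomes are secondary and described as being explored. The reply does not remove the point that the article names a specific test which discards information already being collected.

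**Conclusion.** The point holds as a low-cost gain in precision on secondary outcomes. The stated chi-square or Fisher test is valid, and the primary conclusion, sample size and error rate are untouched. Under the 35%, 80% v 20% and odds ratio 4 assumptions, stratifying by baseline adds about 10 to 11 points of power at 20 per arm and 5 at 17. With phi near 0.2 the change runs from a gain of 2 points at 20 per arm to a loss of 2 points at 17. Even with the gain, these comparisons have low power against moderate effects, so adjustment improves them without making them conclusive. For living status, the conclusion is only that its analysis as an ordered outcome should be stated.

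**What to change.** Replace the sentence on categorical secondary outcomes in Proposed Analyses with wording to this effect:

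- **Binary outcomes with a recorded baseline status:** Mantel-Haenszel test stratified by that status, without continuity correction, or penalized (Firth) logistic regression with the baseline value as covariate. Choose one in advance.
- **Independent living status:** analysed as ordered, with its baseline rating, by a baseline-adjusted ordinal model or a rank test stratified by baseline, and not by a nominal chi-square or Fisher test.
- **Categorical outcomes without a baseline value:** the present chi-square and Fisher rule can stay.

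No new data or visits are needed. The costs are slightly more analysis work, a possible small loss of power if baseline is only weakly prognostic, and an odds ratio that is conditional on baseline. In the worked example the conditional odds ratio of 4 corresponds to a marginal one of (0.654 / 0.346) / (0.41 / 0.59) = 2.7, so the raw proportions by arm should be reported beside it.

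### Categorical secondary outcomes are tested without the enrolment status that the plan collects, which costs precision and leaves the estimate open to chance baseline imbalance (minor)

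*Protocol article*

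**What the plan says.** The Proposed Analyses section of the protocol article treats the two kinds of secondary outcome differently.

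- Continuous outcomes: "analysis of covariance with participants' baseline scores on the secondary outcome measure included as a covariate".
- Categorical outcomes: "categorical secondary outcome measures (e.g., employed vs. unemployed), a chi-square analysis will be used". If its requirements fail, "Fisher's exact probability test [69] with the continuity correction proposed by Overall [70] will be used instead". Neither test has a baseline term.

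The Secondary Outcome Measures section lists the patient measures, among them "social and vocational functioning (Social Functioning Scale: SFS [56"]) and independent living status, for which "subjects' living status will be rated on a 4-point scale". Of these it says: "These measures will be administered when subjects enroll in the study and again after the completion of 12 months of MFG".

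Under Randomization and Treatment Allocation: "Randomization will be completed using a block randomization procedure with blocks of varying sizes". No stratification by employment or living status is mentioned. The planned total is 40 patients, about 20 per arm, of whom 17 per arm are expected to be evaluable.

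**The concern.** For a status measured at both visits, an unadjusted comparison at 12 months counts a patient who was employed throughout the same as one who found work during treatment. If enrolment status predicts later status, two things follow. Variation that the enrolment value could explain stays in the error term, so power is lost. And with about 20 per arm the groups will sometimes differ at entry by chance; that difference carries through to the 12-month table and looks like part of the treatment effect.

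The article does not leave this open for a later document: it names the test and gives the example. The baseline value needed for a better analysis is, on the article's own schedule, already being collected.

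**Working it through.** **Nothing to reproduce.** The article states no power, rate or effect for categorical secondary outcomes. Its sample size concerns relapse only and plays no part here. All rates below are assumptions.

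**1. How often the arms differ at entry.** Take 20 per arm, independent binomial counts and 30%, 40% or 50% employed at entry. An exact calculation gives a difference of 3 or more patients in 38.7%, 42.0% and 43.0% of trials, and of 5 or more in about 12-15%.

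**2. How far the imbalance shifts the estimate with no treatment effect.** Let s be the proportion of those employed at entry who are employed at 12 months, g the proportion of the others who are, and d the entry difference in patients. The expected 12-month difference is (d/20) × (s − g).

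- 9 v 6 (d = 3): 0.15 × (0.70 − 0.30) = 6 points; 0.15 × (0.90 − 0.10) = 12 points.
- 11 v 6 (d = 5): 0.25 × 0.40 = 10 points; 0.25 × 0.80 = 20 points.

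**3. False rejection given the imbalance** (simulation, no effect, two-sided 5%). At 11 v 6 the stated test rejects in about 7-10% of trials, and a Mantel-Haenszel test stratified by entry status in 4-6%. At 9 v 6 the stated test does not over-reject; only the estimate moves.

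**4. False rejection over all randomisations.** In 40,000 simulated trials per scenario with 20 per arm and 40% employed at entry, the chi-square rejects in 4.3-5.0% and the stratified test in 3.4-4.9%.

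**5. Power, same simulation.** The columns give a conditional odds ratio (OR) of 4 or 8 for treatment. Each cell is unadjusted chi-square → stratified test.

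| s / g in control | OR 4 | OR 8 |
|---|---|---|
| 50% / 50% (not prognostic) | 53% → 51% | 81% → 79% |
| 60% / 30% | 48% → 51% | 81% → 82% |
| 70% / 20% | 36% → 46% | 70% → 78% |
| 80% / 20% | 31% → 42% | 63% → 74% |
| 90% / 10% | 14% → 27% | 36% → 60% |

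With a prognostic baseline the gain runs from 1.2 points (80.5% → 81.7%) to 23.8 points (35.8% → 59.6%). Without one, stratifying costs 2 to 3 points. With 17 per arm the pattern is the same but smaller: from −0.3 points (45.3% → 45.0%) to 16.6 points (35.0% → 51.6%).

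**6. Other effect sizes** (20 per arm).

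- A large effect (40% employed at entry; s/g of 85/10 in control and 95/45 with cognitive remediation) gives 33% → 53%.
- A modest effect (80/20 v 85/30) gives 7.0% → 8.9%.
- Few employed at entry (15%; 70/20 v 85/45) gives 33.5% → 36.9%.
- A non-prognostic baseline (50/50 v 75/75) gives 36.9% → 36.0%.

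Steps 4 and 5 use the plain chi-square without the Fisher fallback. In the scenarios where this was checked, the fallback would apply in under 7% of trials, so it does not drive the comparison.

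**The case against.** The strongest reply is that the planned test is valid and the outcomes are secondary and exploratory. That stands. A reader might infer that a chance imbalance inflates the type I error; step 4 shows that it does not. Randomisation holds the overall rate near 5%, and the excess exists only conditional on a marked imbalance. Nor may the 39-43% frequency be read together with the 7-10% rejection rate. The first belongs to differences of 3 or more, the second to 11 v 6, and differences of 5 or more occur in only 12-15% of trials.

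A reader might also take it as stated that employment is recorded at enrolment. It is not. The article schedules the Social Functioning Scale at both visits, and a binary employment item is an inference from that. A vocational result analysed as a scale score would already be adjusted by the analysis of covariance. For living status, rating at both visits is explicit.

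Nor can it be said that the plan's own reason for adjusting extends to binary outcomes. The article gives a citation, not a reason, and the source is not at hand.

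Finally, the gain depends on prognostic strength and effect size, neither of which is documented. With modest effects or a weak baseline it is a few points or slightly negative, and most of the scenarios stay below 80% power either way.

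**Conclusion.** The point holds as a minor one about efficiency and conditional bias, not validity. The article fixes an unadjusted test for categorical secondary outcomes while its schedule supplies an enrolment value and its continuous analyses use theirs.

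The size depends on persistence of status, which is assumed throughout. With 20 per arm and a prognostic baseline, about 1 to 24 points of power are forgone; with a non-prognostic one, the unadjusted test is better by about 1 to 3. A chance entry imbalance shifts the estimate by 6-12 points at 9 v 6 and by 10-20 points at 11 v 6, and only the latter brings over-rejection. The primary outcome, relapse, is unaffected.

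**What to change.** In Proposed Analyses, replace the sentence on categorical secondary outcomes by wording to this effect:

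- Binary secondary outcomes measured at enrolment and at 12 months will be compared by a Mantel-Haenszel test stratified by enrolment status, with the Mantel-Haenszel risk difference and its 95% confidence interval. An exact stratified test, or penalised logistic regression with enrolment status as a covariate, will be used if counts are sparse.
- The 4-point independent living status will be compared by an ordinal analysis adjusted for the enrolment rating, or by a stratified rank (Cochran-Mantel-Haenszel) test, with sparse categories collapsed by a rule set in advance.
- The unadjusted 12-month table will be shown as description.

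The article should also say whether employment is recorded as a status at enrolment. Ordinary logistic regression is best avoided here, because separation is a real risk with 40 patients.

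The cost is a few lines of text, with no new visits or patients, and no new data if employment is already recorded at enrolment. The downside is sparse strata if nearly everyone has the same status at entry, and little or slightly negative gain if that status predicts poorly. The choice should be fixed before outcome data are seen.
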